### Primary outcome: successful to cognitive training

The effect of training has been measured by evaluating some specific cognitive indicators after the application of effective mnemonics and techniques on cognitive performance.

The study involved the evaluation of subjects who succeed positively to cognitive training. Each group was differently assessed, choosing different outcomes [19, 20].

The first outcome to evaluate the enhancement of cognitive performance in subjects with AD was calculated using ADAS [21]. A decrease in the total score of ADAS of at least two scores measured after the cognitive intervention was an indicative of the enhancement of cognitive performance.

For HE, the first outcome was calculated using the “List of Words” [25]. An increase of 1.5 words in this test measured after the intervention was an indicative of the enhancement of cognitive performance. For MCI subjects, an increase in score of 0.5 of “Word Pairs Learning Test” [27], was taken into account.

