### Sample size calculation

It was based on the null hypothesis that proportion of “success” and “failure” to the intervention is equal in the two groups of subjects (i.e. EG and CG), such as OR = 1.

Success and failure were defined differently for each group of subjects (i.e. HE, MCI, AD) on the basis of a significant variation in the primary outcomes (see below).

Considering an OR = 1.5 indicative of an effect of cognitive training, a total sample of 300 subjects (i.e. 100 subjects per group) allow to reach a 90 % of statistical power using logistic regression at the 5 % level (two-tailed). Drop-out rate was set at 20 %; indeed, a total of 321 subjects were recruited.

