### Statistical analysis

Analysis will be carried out by the software SPSS 16 (SPSS Inc. Chicago, Illinois), separately for each group of subjects and across groups.

Descriptive analysis will be used to check the distribution of the data. Bivariate analysis will be used to compare within each group the characteristics of experimental and control groups, by chi-square for frequencies and *t* test for continuous variables. Paired tests will be used to check for the variation in cognitive measures before and after intervention within each group. General linear models will be used to verify the effect of intervention in the outcome measures, adjusting for covariates.

Each subject will be classified on the basis of primary outcomes and then included in multiple logistic regression models to identify the predictors of improvements in cognitive status, adjusting for covariates. Repeated-measures ANOVA will be used to examine the training effect on biochemical parameters adjusted for age and sex. The significance level will be set at *P* < 0.05.

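### Primary outcome cuts cognitive test scores into success or failure at fixed raw gains, which costs a third or more of the information; make the baseline-adjusted score primary

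*Protocol article*

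**What the plan says.** The section on the primary outcome in the protocol article sets one rule per cognitive group:

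- AD: "A decrease in the total score of ADAS of at least two scores measured after the cognitive intervention"
- HE: "An increase of 1.5 words in this test measured after the intervention", on the List of Words
- MCI: "For MCI subjects, an increase in score of 0.5 of “Word Pairs Learning Test"

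Two citations support the choice of outcomes. The text gives no reason for the cut-offs themselves.

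The sample size section takes as its null hypothesis that the proportion of successes "is equal in the two groups of subjects (i.e. EG and CG), such as OR = 1". It continues "Considering an OR = 1.5 indicative of an effect of cognitive training" and concludes that "a total sample of 300 subjects (i.e. 100 subjects per group") gives 90% power with logistic regression at two-sided 5%.

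The statistical analysis section states: "Each subject will be classified on the basis of primary outcomes and then included in multiple logistic regression models", adjusted for covariates. The paragraph before it also plans general linear models for the effect of the intervention on the outcome measures, adjusted for covariates. Those models are not called primary, do not underlie the sample size, and do not name the baseline score as a covariate.

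The neuropsychological assessment section schedules the battery at baseline and at all three follow-ups. Table 1 of the article lists each primary test for its group.

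**The concern.** All three primary measures are numerical scores. Reducing them to success or failure treats a subject just short of the cut like one who deteriorated sharply, and one just past it like one who improved greatly. The class is also built on raw change, which is less efficient than the follow-up score adjusted for baseline unless the two correlate almost perfectly.

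The direction of the cut matters as well. In AD and MCI, benefit may take the form of less decline. A trained subject who stays stable while comparable controls worsen is a failure under these rules. The introduction treats preventing or delaying decline as important, and follow-up runs to 2 years, when control decline is most likely to matter.

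At stake is power in a trial with about 100 subjects per cognitive group.

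**Working it through.** **Inputs from the article.** OR = 1.5, two-sided 5%, 90% power, 300 in total, 100 per cognitive group.

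**Assumed, because the article gives no figure.** Normal scores with equal SDs, 1:1 allocation (50 per arm in each cognitive group), no losses, control success 20-50%, baseline-to-follow-up correlation r = 0.6-0.8.

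**1. The plan's own figure.** Two-proportion power is Φ{(|p2 − p1| − 1.96·√[2p̄(1 − p̄)/n]) / √[(p1(1 − p1) + p2(1 − p2))/n]}, with n per arm.

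- With 150 per arm, power at OR 1.5 is at most about 42% at any control rate tried from 10% to 50%.
- With 50 per arm it is at most about 17%.
- 90% power needs at least 1,026 subjects per comparison.
- The stated 90% is approached only with the formula for a continuous predictor, OR per SD, and a success rate near 0.3: N = (1.96 + 1.28)²/(0.3 × 0.7 × (ln 1.5)²) ≈ 304. That is not the EG-CG hypothesis the article states.

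**2. Information lost by the cut.** For success rate p and cut c, with φ the normal density, efficiency against the change score is φ(c)²/[p(1 − p)]. Change has variance 2σ²(1 − r). The follow-up score adjusted for baseline has residual variance σ²(1 − r²). Their ratio is (1 + r)/2, which multiplies the efficiency when the comparator is the adjusted score.

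| p | φ(c) | against change score | against adjusted score, r = 0.6 to 0.8 |
|---|---|---|---|
| 0.2 | 0.280 | 0.49 | 0.39-0.44 |
| 0.3 | 0.348 | 0.58 | 0.46-0.52 |
| 0.4 | 0.386 | 0.62 | 0.50-0.56 |
| 0.5 | 0.399 | 0.64 | 0.51-0.57 |

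The loss is therefore 36-51% against the change score and 43-61% against the adjusted score.

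**3. Power at the planned effect (p1 = 0.30, r = 0.7, 50 per arm).**

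- OR 1.5 gives p2 = 0.391. The equivalent shift is Φ⁻¹(0.391) − Φ⁻¹(0.30) = 0.248 SD of change.
- Responder test: (0.091 − 1.96 × 0.0951)/0.0947 = −1.00, so power is 16%.
- Adjusted score: residual SD √0.85 = 0.922 and standard error 0.922 × √(2/50) = 0.184. Then 0.248/0.184 − 1.96 = −0.61, so power is 27%.
- Simulation gives 16-17% against 26%.
- For 90% power the responder test needs 1,138 subjects and the adjusted score 580. Over all the assumed rates and correlations the ranges are 1,038-1,432 and 524-674.

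**4. Power at a larger effect (0.4 SD of the score, same setting).**

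- SD of change is √(2 × 0.3) = 0.775, so the shift is 0.4/0.775 = 0.516 SD of change. Then p2 = 0.497 and OR ≈ 2.3.
- Simulated power is about 54% (responder) against 78% (adjusted score).
- Adding the baseline score to the logistic model recovers at most about 5 percentage points. The loss comes from the cut.

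**5. Slowed decline in AD.** Assume a change SD of 4 points, a true benefit of 2 points, r = 0.7 and 50 per arm. If controls worsen by w points, success rates are 1 − Φ((2 + w)/4) in controls and 1 − Φ(w/4) in trained subjects.

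| w | control | trained | responder power | adjusted-score power |
|---|---|---|---|---|
| 0 | 0.309 | 0.500 | 50% | 77% |
| 2 | 0.159 | 0.309 | 42% | 77% |
| 4 | 0.067 | 0.159 | 30% | 77% |

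With a change SD of 6 the responder figures are 26%, 24% and 21%, against 44%.

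**The case against.** The strongest reply is that the scores are not thrown away. The statistical analysis section already plans covariate-adjusted linear models on the outcome measures and gives the logistic models the task of finding predictors of improvement. A reader might infer that the plan has no continuous analysis; the text does not support that. What stands is that the declared primary outcome, its null hypothesis and the sample size all use the cut, and that the linear models have no stated rank.

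A reader might also infer that the trial cannot show slowed decline. That is too strong. Step 5 shows reduced power, not zero power. The tests are repeated at every follow-up, and conversion from MCI to dementia is a secondary outcome. Nor is slowing decline the declared primary aim. The sentence in the introduction is general background, and the stated aims concern performance and improvement of cognitive functions, which a gain-based outcome fits.

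The cut-offs cannot be called too small relative to measurement error. The article gives no SD or retest reliability, and the cited sources are not at hand. The efficiency argument does not depend on this.

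Finally, the larger gains in power occur at odds ratios above the planned one. At OR 1.5 both analyses are badly underpowered.

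**Conclusion.** The point holds as a matter of efficiency and of fit to slowed decline. The responder analysis is valid but wasteful. The direction of the loss is certain. Its size depends on success rates and correlations that the article does not state, but it exceeds one third in every case tried between 20% and 50% success. At the planned OR of 1.5 with 50 per arm, the adjusted score raises power from 13-17% to 24-29% over the assumed ranges. It would be wrong to conclude that the change repairs the sample size: that shortfall is a separate fault and remains.

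**What to change.** Before outcomes are compared by arm, amend the primary outcome and statistical analysis text as follows:

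- Within each cognitive group, the primary analysis is the EG-CG difference in the follow-up 1 score (ADAS for AD, Word Pairs for MCI, List of Words for HE), with 95% CI. It comes from the already planned linear model, with arm and baseline score as terms.
- The same model at follow-ups 2 and 3 is secondary. This is where slowed decline would show.
- The success proportion under the present cut-offs stays as a supportive responder analysis.

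No new data are needed. There are two costs. The headline becomes a mean difference instead of a percentage of responders. The change also departs from the responder definition behind the sample size at a time when the article describes the follow-ups as already carried out, so it must be dated, justified and disclosed to avoid looking like a choice made after seeing results. The 90% power statement should not be carried over to the new primary analysis.

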### Secondary outcomes

They includeThe assessment of the effects of intervention and the relationship between psychological status, lifestyle characteristics, functional and health status, biochemical aspects by the use of a multidisciplinary approach.The investigation of rate of percentage of subjects with MCI who converted to dementia.The identification of biochemical markers correlated with the cognitive training in HE, MCI, AD.

### Neuropsychological assessment before and after cognitive training

A comprehensive neuropsychological test battery was conducted in all participants at pretest (baseline) and at the three phases of follow-up. The assessment of cognitive and psychological status included many instruments, as indicated in Table 1.

**Table 1 Tab1:** List of assessment instruments by group

Instruments	HE	MCI	AD
Overall cognitive status			
MMSE [22]	^a^	^a^	^a^
Memory			
Supra-span of Corsi [23]	n.a.	^a^	^a^
Backward and forward verbal span [24, 25]	^a^	^a^	^a^
List of words [25]	^a^	n.a.	n.a.
Prose memory test [26]	n.a.	^a^	^a^
Word pairing learning test [27]	n.a.	^a^	^a^
Attention			
Attentive matrices [26]	^a^	^a^	^a^
Language and executive functions			
SVF and PVF [28]	^a^	^a^	^a^
Cognitive decline in dementia			
ADAS [29]	n.a.	n.a.	^a^
Overall severity			
CDR [30]	n.a.	^a^	^a^
Psychological assessment			
GDS-30 [31]	^a^	^a^	^a^
PSS [32]	^a^	^a^	n.a.
Questionnaire of well-being [33]	^a^	^a^	n.a.
MAC-Q [34]	^a^	^a^	n.a.
Questionnaire of confidence [33]	^a^	n.a.	n.a.
Functional status			
ADL [35]	^a^	^a^	^a^
IADL [36]	^a^	^a^	^a^
Social networks			
LSNS [37]	^a^	^a^	^a^
Lifestyle			
Lifestyle questionnaire	^a^	^a^	^a^
PASE [38]	^a^	^a^	^a^

*n.a.* not applicable for this group

^a^Applicable for this group

### Intervention

The programme lasted about 2 months for each subject. The main aim of the intervention was to improve different cognitive functions, in order to activate and to motivate participants to ameliorate their cognitive health behaviour by remaining cognitively active and compensating deficits with learned mnemonic strategies after training.

Different comprehensive training methods have been applied to the different groups of subjects, on the basis of their cognitive status. We focalized the intervention not only to cognitive enhancement, but also on many aspects such as advice and psycho-education about healthy lifestyle strategies to maintain cognitive reserves and engagement in leisure activities. Training has been applied for subjects with MCI and with mild–moderate AD using an individualized approach to help them to identify their individual goals and practise strategies focused on them.

The intervention for HE consisted of 10 sessions of 90 min in groups of about 10 participants, once a week. The LAB-I methodology [33], which includes the learning of some effective mnemonics and techniques (such as visual imagery, creation of stories, mental associations, remembering word lists and sequences of items), was used. The addressed domains were, in particular, working memory and learning processes. According to the latter methodology that uses a metacognitive and motivational approach, the participants were also required to perform at-home exercises each day prior to the subsequent session. Another important aim of this enhancement training is focused on maximizing social participation.

MCI group received an individual comprehensive multi-modal training of 10 individual sessions of 45 min, once a week, which included psycho-education about memory loss, and restorative and compensatory cognitive training, which consists of learning strategies for orientation, memory, categorization and clustering. Since MCI subjects often present level of anxiety, stress and/or depression, due to their consciousness of cognitive decline, the effect of metacognition was evaluated to analyse their role on cognitive performances.

AD group received a comprehensive intervention of 10 individual sessions of 45 min each, once a week, including restorative cognitive training addressed in particular to the empowerment of attention functions, orientation, planning of activities of daily living and episodic and prospective memory. Another aim of intervention was to decrease functional disability maximizing engagement in activities of daily living and healthy lifestyle and to support patients and their caregivers for psychological disorders. Participants were also asked to perform homework exercises each day with the help and support of a caregiver.

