**Methods:**

The study is a prospective randomized intervention for the assessment of cognitive training effects in three groups of elderly subjects with different cognitive status. A total of 321 elderly people were enrolled in Marche Region, Italy. Each subject was randomly assigned to an experimental group or to a control group. Cognitive performances and biochemical blood markers have also been analysed before cognitive training (baseline), immediately after termination (follow-up 1), after 6 months (follow-up 2) and after 2 years (follow-up 3).

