### Sample

Three hundred and twenty-one community-dwelling elderly subjects (aged ≥65 years) living in Marche Region were enrolled and divided into three groups, according to their cognitive status: 111 subjects without relevant cognitive diseases (HE), 109 subjects with MCI and 101 subjects affected by mild–moderate AD.

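### Healthy elderly (HE) are trained in classes of about 10, but the named post-training analyses have no class term; if outcomes correlate within classes, HE standard errors will be too small

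*Protocol article*

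**What the plan says.** On delivery, the Intervention section of the protocol article says for the healthy elderly: "The intervention for HE consisted of 10 sessions of 90 min in groups of about 10 participants, once a week". The other two groups are trained one to one: "MCI group received an individual comprehensive multi-modal training of 10 individual sessions of 45 min, once a week" and "AD group received a comprehensive intervention of 10 individual sessions of 45 min each, once a week".

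On allocation, the abstract says: "Each subject was randomly assigned to an experimental group or to a control group". The Sample section gives "111 subjects without relevant cognitive diseases (HE), 109 subjects with MCI and 101 subjects affected by mild–moderate AD". The split between experimental group (EG) and control group (CG) within HE is not given.

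On analysis, the Statistical analysis section says: "General linear models will be used to verify the effect of intervention in the outcome measures, adjusting for covariates". It also names multiple logistic regression on subjects classified by the primary outcome, paired before–after tests, repeated-measures ANOVA for the biochemical parameters (adjusted for age and sex), and chi-square and t tests to compare EG and CG characteristics. Analyses are run within each cognitive group and across groups. No random effect, clustered variance or other allowance for training class is named, and the Sample size calculation section contains no ICC or design effect.

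**The concern.** This is a partially nested design: subjects are randomised one by one, but HE subjects in the experimental arm then spend 10 weekly sessions in the same class. Class members share sessions, peers and calendar time, so their outcomes may be more alike than those of people in different classes. The link to the primary outcome is direct. The HE course teaches, among other things, the recall of word lists, and HE success is a gain of 1.5 words on the List of Words test. A class that is taught well, or that works well together, could move several successes at once.

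The named models, in their ordinary form, treat each subject as an independent observation. With positive within-class correlation they overstate the information in the experimental arm. The HE training effect would then be declared significant too often, with confidence intervals that are too narrow. Pooled analyses that include HE would carry part of the same error.

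**Working it through.** **The plan's own figure.** The article states: "a total sample of 300 subjects (i.e. 100 subjects per group) allow to reach a 90 % of statistical power using logistic regression at the". The test is two-tailed with alpha 0.05, for an odds ratio of 1.5. That figure makes no allowance for classes, and it does not reproduce for an EG–CG contrast even without them. With an assumed control success rate of 0.45, the EG rate is 0.551. The usual two-proportion formula then gives n per arm = (1.96·√(2·0.5005·0.4995) + 1.282·√(0.45·0.55 + 0.551·0.449))² / 0.101² ≈ 513, or about 1,026 in total. That was the lowest total found at assumed control rates from 0.1 to 0.6. This is a separate problem, and the class point does not depend on it.

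**Inputs**
- Class size m = 10 (Intervention section).
- HE total 111 (Sample section). With 1:1 allocation, which is an assumption, EG has 111/2 = 55.5 subjects and 55.5/10 ≈ 5.6 classes, so 5–6.
- ICC not given. Assumed range 0.01 to 0.20.
- Controls taken as unclustered. This is also an assumption, since the text does not describe the control condition.

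**Formulas**
- Design effect in EG: DE = 1 + (m − 1)·ICC. In CG it is 1.
- Variance ratio of the EG–CG difference, true to planned: V = (DE + 1)/2 at 1:1.
- Planned standard error too small by 1 − 1/√V.
- True two-sided type I error: 2·[1 − Φ(1.96/√V)].

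**Example, ICC 0.05.** DE = 1 + 9·0.05 = 1.45. V = 2.45/2 = 1.225. √V = 1.107. The planned standard error is 1 − 1/1.107 ≈ 10% too small. 1.96/1.107 = 1.77, so the type I error is 7.7%. The effective EG size is 55.5/1.45 ≈ 38.

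| Assumed ICC | DE in EG | True SE / planned SE | Planned SE too small by | True type I error |
|---|---|---|---|---|
| 0.01 | 1.09 | 1.02 | 2% | 5.5% |
| 0.02 | 1.18 | 1.04 | 4% | 6.1% |
| 0.05 | 1.45 | 1.11 | 10% | 7.7% |
| 0.10 | 1.90 | 1.20 | 17% | 10.4% |
| 0.20 | 2.80 | 1.38 | 27% | 15.5% |

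**Simulation.** Two simulations checked the normal approximation: 6 classes against 56 controls (4,000 runs per ICC), and 5 classes of 11 against 56 controls (20,000 runs). At ICC 0.02 / 0.05 / 0.10:
- t test: 6.1 / 7.5 / 9.4% and 5.9 / 7.9 / 11.4%.
- Test on a success/failure outcome, which is closer to the primary analysis: 5.3 / 7.0 / 8.7% and 6.6 / 7.6 / 9.7%.

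With ICC 0, the rates that were run lay between 4.8% and 5.4%. For the success endpoint, a fair summary is about 5–7%, 7–8% and 9–10%.

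**Sensitivity**
- Classes of 8 or 12 at ICC 0.05 give 7.1% or 8.3%.
- If controls also met in groups of 10, V = DE and the type I error is 7.1 / 10.4 / 15.5% at ICC 0.02 / 0.05 / 0.10.
- The same three values apply to a paired test run in the HE experimental arm alone, if the ICC refers to the change score.
- To keep the information of 100 independent HE subjects, 100·V subjects are needed: about 109, 123 and 145.

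**The case against.** **The ICC is unknown and may be near zero.** This stands, and it makes the finding conditional. A reader might infer that the HE standard errors are certainly too small. The article gives nothing from which to estimate a within-class correlation, and at 0.01–0.02 the excess error is about half a point to one point.

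**A condensed article may leave variance estimation to an analysis plan.** This stands in part. A logistic model with a clustered variance is still logistic regression, and the covariates are not listed. But the article does name its model families, including a correlated-data method for the biochemical repeats, and names nothing for class. An ordinary class covariate would not help, because class is nested in the experimental arm and is confounded with it.

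**Not every planned test is affected.** This stands. The chi-square and t tests compare the characteristics of EG and CG. Where they are done at baseline, before any class has met, they are unaffected.

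**HE may not be the only group with shared influences.** This stands. A reader might infer that HE alone has the problem and will look more certain than MCI and AD. The article does not say how many trainers there were or who taught whom, so subjects trained individually may also share a trainer.

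**The social aim proves little.** The article says "Another important aim of this enhancement training is focused on maximizing social participation", but this may mean social life in general and not interaction within the class. The case for correlation rests on the shared sessions and the word-list content.

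**The control arm and the split are not described.** This stands. The flow chart is not available, so unclustered controls and 1:1 allocation are both assumptions.

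**Conclusion.** The mismatch is on the face of the article: class delivery for HE subjects in the experimental arm, and named post-training analyses without a class term. Whether it produces bias, and how much, depends on an ICC that the article does not give. It is minor at 0.01–0.02 and material from about 0.05, where the true type I error is about 7.7% for the EG–CG difference and about 7–8% for the success endpoint. The table's standard-error ratios should be read with care: at ICC 0.10 the true standard error is 20% larger than planned, which means that the planned one is 17% too small, not 20%.

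The conclusion covers post-training HE comparisons and pooled analyses that include HE. It assumes classes of about 10, 1:1 allocation and controls who did not meet in groups. It does not extend to baseline comparisons, and it does not support a claim that MCI and AD are free of comparable correlation. The point should be corrected, but it does not invalidate the trial.

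**What to change.** 1. Keep the training-class identifier for every HE subject in the experimental arm. The article does not say whether it was recorded, so confirm this first.
2. For continuous post-training HE outcomes, including the biochemical parameters, replace the independent-subjects model with a partially nested mixed model. It should have a random class effect in the experimental arm only, each control as a singleton unless controls also met in groups, and small-sample degrees of freedom. Repeated visits still need their within-subject correlation.
3. For the HE success endpoint, use an equivalent clustered analysis with a small-sample correction. Uncorrected cluster-robust errors are unreliable with 5–6 classes.
4. Carry the same class term into paired tests in the HE experimental arm and into pooled analyses that include HE.
5. State what HE controls received and whether they met in groups, and report the ICC with its interval.

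The Statistical analysis section is written in the future tense, so this is a change of model and needs no new data beyond class membership. Whether the named software version can fit these models should be checked. The costs are wider HE confidence intervals, few degrees of freedom, and an ICC that 5–6 classes will estimate imprecisely.
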